## Abstract

**Introduction:**

Arginine vasopressin (AVP) and oxytocin (OXT) are both hormones released from the posterior pituitary. While AVP primarily regulates water reabsorption in the kidneys, OXT plays a key role in socioemotional functioning. Due to the anatomical proximity, disruptions of the AVP system leading to AVP deficiency (AVP-D) may also affect the OXT system, possibly resulting in an additional OXT deficiency. This hypothesis was recently proven by using the 3,4-methylenedioxymethamphetamine stimulation tests and identifying OXT deficiency in patients with AVP-D, linked to increased anxiety and impaired emotion recognition. Despite these findings, OXT replacement therapy is not currently established as a treatment for AVP-D and long-term replacement therapy remains unexplored.

**Methods and analysis:**

This is a randomised, double-blind, placebo-controlled, parallel-group trial enrolling adults with AVP-D. Participants are randomised 1:1 to receive intranasal OXT (Syntocinon, 24 IU twice daily) or placebo for 28 days. The primary endpoint is a composite binary outcome defined as a clinically meaningful improvement in either trait anxiety (≥5-point reduction in State-Trait Anxiety Inventory-Trait Score) or emotion recognition (≥4-point increase in EmBody/EmFace task performance). Secondary outcomes include empathy, stress reactivity, neuroimaging markers of amygdala activity, additional psychological measures, metabolic parameters and safety outcomes, including hyponatraemia. Analyses will follow the intention-to-treat principle, with Fisher’s exact test used for the primary outcome and mixed-effects models for secondary endpoints.

**Ethics and dissemination:**

The study has been approved by the competent ethics committees and regulatory authorities in Switzerland and the European Union. The following institutions granted ethical approval: Ethikkommission Nordwest- und Zentralschweiz (EKNZ), project number EKNZ 2023–01010 and the Erasmus MC MERC, EU-CT number 2024–5 16 813-19-00. Results will be published in open-access, peer-reviewed journals and disseminated via scientific meetings, media communication and lay summaries provided to participants. De-identified individual participant data will be made available on reasonable request following publication.

**Trial registration number:**

NCT06036004.

STRENGTHS AND LIMITATIONS OF THIS STUDYThe study uses a patient-centred design, with extensive patient and public involvement informing endpoint selection, study design, feasibility and outcome prioritisation, thereby enhancing clinical relevance and acceptability.A key limitation is the moderate sample size, inherent to rare-disease research, which may limit power for subgroup analyses and detection of small effect sizes, particularly for secondary and exploratory outcomes.The reliance on subjective psychological measures (eg, anxiety and empathy questionnaires) may introduce response variability; however, this is mitigated by the use of validated instruments and complementary objective computerised emotion-recognition tasks.Self-administration of the investigational medicinal product may lead to variability in adherence, which could affect treatment effects, although adherence will be monitored through diaries and medication accountability.

## Background

 Arginine vasopressin (AVP) and oxytocin (OXT) are closely related nine-amino acid neuropeptides.^1 2^ Both are synthesised in the hypothalamic supraoptic and paraventricular nuclei and released from the posterior pituitary.^1 2^ While AVP primarily regulates water balance, OXT plays a crucial role in regulating socioemotional behaviours, including attachment, fear reduction and emotion recognition.^1 3^

Disruption of the hypothalamic-pituitary axis due to tumours, inflammation or trauma can lead to AVP deficiency (AVP-D), formerly known as central diabetes insipidus, clinically characterised by hypotonic polyuria and polydipsia.^1 4^ Although desmopressin, an AVP receptor analogue, effectively controls these symptoms, patients frequently experience persistent psychological symptoms and impaired quality of life (QoL).^5^ Importantly, these findings on psychological symptoms are consistent across both, patients with isolated AVP-D and those with additional anterior pituitary dysfunction, therefore challenging the assumption that anterior pituitary hormone deficiencies alone contribute to these psychopathological changes.^5 6^ Given the structural proximity of AVP and OXT systems, disruptions causing AVP-D could also disrupt OXT production, potentially leading to a coexisting OXT deficiency. This disruption in the OXT system may—at least partially—explain the psychological symptoms observed in patients with AVP-D. This hypothesis is supported by 3,4-methylenedioxymethamphetamine (MDMA) stimulation tests, where healthy individuals exhibited an eightfold increase in OXT secretion, while patients with AVP-D showed no relevant OXT response.^7 8^ Importantly, in contrast to healthy controls, patients with AVP-D demonstrated reduced trust, impaired fear reduction and diminished recognition of positive emotions on MDMA stimulation, reinforcing the link between OXT deficiency and psychological impairments in this population. Despite these findings, OXT replacement therapy is not currently established as a treatment for AVP-D. Limited data from a single small study suggest that a single dose of intranasal OXT may improve emotion recognition, but its long-term effects remain unexplored. This randomised, placebo-controlled, double-blind trial aims to evaluate intranasal OXT therapy as a novel approach to improving psychological symptoms and socioemotional functioning in patients with AVP-D.

Intranasal OXT is the most commonly used formulation in behavioural research, as it enables partial direct brain delivery via olfactory and trigeminal pathways and is widely applied in human studies.^9^ Standard adult dosing in behavioural studies is 24 IU per administration, with reported doses ranging from 8 IU to 84 IU, and evidence suggesting a non-linear, inverse U-shaped dose–response with maximal central effects at 24 IU.^10 11^ In this study, Syntocinon (40 IU/mL) will be administered at a total daily dose of 48 IU, given as 24 IU twice daily (three puffs per nostril per dose). This regimen aligns with established dosing shown to increase cerebrospinal fluid OXT and modulate central emotional processing.

## Methods

### Study design

This is a randomised, double-blind, placebo-controlled, parallel-arm trial investigating the effects of intranasal OXT compared with placebo in patients with AVP-D (figure 1). The trial includes a 28-day treatment period, with patients randomised to receive either intranasal OXT (24 IU twice daily) or placebo. Participants will attend study visits on screening/day 0, day 1 and day 28 (±2). Optional substudies at day 14 will include fMRI (functional Magnetic Resonance Imaging) assessments and social-stress testing.

**Figure 1 F1:**
[figure not shown]
Main research question. AVP, arginine vasopressin; OXT, oxytocin; QoL, quality of life.

The trial is currently conducted at the University Hospital Basel, Switzerland, and Erasmus Medical Centre Rotterdam, the Netherlands, with additional study centres planned in Berlin, Germany and Lyon, France. Trial details are published on *Clinicaltrials.gov (NCT06036004) and Clinical Trials Information System (EUCT 2024–5 16 813-19-00*). The study protocol (V.5.0 (01.02.2025)) was approved by the relevant ethics committees and competent regulatory authorities in accordance with national and international regulations. In Switzerland, approval was obtained via the BASEC system (Business Administration System for Ethics Committees) from the competent Cantonal Ethics Committee (Ethikkommission Nordwest- und Zentralschweiz, No. 2023–01010) and Swiss Agency for Therapeutic Products (SwissMedic, No. 701718), and in the European Union, the study was authorised through the Clinical Trials Information System by the relevant national authorities (EUCT 2024–5 16 813-19-00). This study will be conducted in compliance with the protocol, the current version of the Declaration of Helsinki, ICH-GCP (International Council for Harmonisation – Good Clinical Practice), as well as all national legal and regulatory requirements.

### Eligibility criteria

See table 1 for the inclusion and exclusion criteria.

**Table 1 T1:** Inclusion and exclusion criteria

Inclusion criteria	Exclusion criteria
Adult patients aged over 18 years with a confirmed diagnosis of AVP deficiency based on accepted criteria	Participation in a trial with investigational drugs within 30 days
Heightened anxiety levels (STAI-T subscale ≥39 score points) or alexithymia levels (TAS-20 total ≥52 score points)	Active substance use disorder within the last 6 months
Stable hormone replacement therapy for at least 3 months with desmopressin and, in case of additional anterior pituitary deficiencies, with the respective substitution therapies	Consumption of alcoholic beverages >15 drinks/week
	Current or previous psychotic disorder (eg, schizophrenia spectrum disorder)
	Pregnancy and breastfeeding within the last 8 weeks
	Unwilling to use an effective hormonal or mechanical form of contraception throughout the study period (female of childbearing potential only)
	Prolonged QTc-time >470 ms assessed with a 12-lead ECG

AVP, arginine vasopressin; QTc, corrected QT interval; STAI-T, State-Trait Anxiety Inventory-Trait; TAS-20, Toronto-Alexithymia Scale.

### Screening, recruitment and informed consent procedure

Participants will be recruited through endocrinologist referrals, electronic health records, online patient platforms, and previous or ongoing diagnostic studies for AVP-D. After initial contact and receiving brief information by telephone, potential participants will receive the patient information sheet and informed consent form by post or email. An example of the participant consent form is provided in the supplemental material. Interested patients may then contact the investigators to ask questions and arrange further evaluation.

At the screening visit, a study physician will explain the nature, purpose, procedures, duration, and potential risks and benefits of the study. Written informed consent will be obtained prior to any study-specific procedures. Screening assessments will include medical history, physical examination, standardised blood pressure measurement, body weight and height, and routine laboratory testing (blood chemistry, haematology and urine pregnancy test). A 12-lead ECG will be performed after at least 5 min of supine rest to exclude QT prolongation, with QT intervals corrected using Bazett’s and Fridericia’s formulas. Anxiety and alexithymia will be assessed using the State-Trait Anxiety Inventory-Trait (STAI-T) and Toronto-Alexithymia Scale (TAS-20) questionnaires, respectively. Participants meeting inclusion thresholds (≥39 in the STAI-T or ≥52 in the TAS-20)^12 13^ will subsequently undergo a standardised neuropsychiatric evaluation using the Mini-International Neuropsychiatric Interview and the Structured Clinical Interview for DSM-5 (Diagnostic and Statistical Manual of Mental Disorders, Fifth Edition) to screen for Axis I and II psychiatric disorders and a history of illicit substance dependence. All study physicians will receive dedicated training by a psychologist prior to study initiation to ensure standardised and consistent administration of these assessments. Final eligibility will be determined based on the combined clinical and psychiatric evaluation. Randomisation takes place immediately after completion of the screening visit, once a participant has been confirmed to fulfil all eligibility criteria and has provided written informed consent (figure 2).

**Figure 2 F2:**
[figure not shown]
Study flow chart. AQ, Autism-Spectrum Quotient Test; BDI-II, Beck Depression Inventory; OXT, oxytocin; PP-QoL, Posterior Pituitary QoL Questionnaire; QoL, quality of life; TAS-20, Toronto-Alexithymia Scale.

### Randomisation and blinding

Participants will be randomised 1:1 to receive either intranasal OXT (Syntocinon) or placebo using the secure secuTrial system, employing block randomisation with a fixed block size of four and no stratification factors, to ensure balanced allocation over time while maintaining allocation concealment. Each randomisation number will correspond to a treatment package containing eight intranasal sprays (5 mL each) for a dosing regimen of 24 IU twice daily over 28 (±2) days.

The randomisation list is generated by the pharmacy and held by the Department of Clinical Research, Basel, and is concealed from participants, investigators, study nurses, study physicians, study psychologists and all outcome assessors. These individuals remain blinded throughout the trial.

Because the container systems of the OXT and placebo sprays differ slightly in appearance, unblinded study personnel, who are not involved in outcome assessments or clinical evaluations, are responsible for medication storage and dispensing. Participants are explicitly instructed not to show or discuss their study medication with blinded study personnel.

The placebo spray contains 0.9% sodium chloride with aromatic scenting to minimise sensory differences. With these procedures, blinding of participants and all personnel involved in clinical care, assessments and data analysis is maintained to ensure methodological rigour.

Emergency unblinding is foreseen in case of a positive urine pregnancy test in one of the main visits. In such a situation, the pregnancy will be confirmed by a blood test, further participation is not allowed, and the participant will be excluded. The online trial database secuTrial provides an emergency unblinding option which will be activated in agreement with the principal investigator in such case.

### Study intervention

#### Intervention group

This study will administer intranasal OXT spray, containing 40 IU of synthesised OXT per mL in a solution optimised for nasal absorption. Each spray delivers 4 IU of OXT per 0.1 mL, with each bottle containing 5 mL (200 IU total). [name] AG, Switzerland, will compound and supply the OXT spray under Good Manufacturing Practice standards. Participants will receive 48 IU of OXT daily, divided into two doses (24 IU in the morning and 24 IU in the afternoon), with three sprays per nostril administered per dose. Study personnel will instruct participants on administration techniques, emphasising a 45 s interval between sprays, and will provide dosing handouts and diaries to facilitate adherence tracking.

#### Control group

The placebo spray will be visually identical in size, volume and labelling but will differ in container system. It will contain 0.9% sodium chloride along with water for injection, disodium phosphate dodecahydrate, edetate disodium dihydrate and benzalkonium chloride. Each spray delivers 0.1 mL of placebo solution, with each bottle containing 5 mL. Packaging and labelling will ensure the sprays are indistinguishable to blinded study personnel.

#### Storage conditions

Investigational products are kept in a secure, limited-access storage area under recommended storage conditions at 2°C to 8°C in the refrigerator before opening. The bottle should be kept at room temperature (15°C to 25°C) after opening.

#### Blinding and dispensing

The dispensing of medication will be handled by unblinded study personnel. Participants will be instructed not to show their study medication to blinded personnel. Used and unused study medications will be returned to the unblinded personnel.

#### Modification, preventive measures and concomitant treatments

No dose modification is intended. No rescue medication for the trial participants is foreseen. In case of necessity of additional treatments during the intervention period, the participants will be instructed to document this in the drug-diary and inform the investigators accordingly. No concomitant care beyond the intervention is planned. Patients must be on stable hormone replacement therapy with desmopressin and, in case of additional anterior pituitary deficiencies, with the respective substitution therapies for at least 3 months before participation. If a change in replacement therapy is needed, each case will be discussed with the study team, and a possible change will preferably be planned before inclusion in the trial and there will be a wait of 3 months for stability. Concomitant psychotherapy (eg, medical therapy with psychotropics, behavioural therapy) is only allowed if this is established for at least 3 months before study inclusion and no discontinuation is planned during the intervention.

The first dose of the study medication will be given the day after successful inclusion. After that, study medication will be administered by the patient in the morning and afternoon daily at home. The empty carton containers with the eight sprays of the study medication must be returned to the investigator for compliance control at the follow-up visit on day 28 (±2). In addition, patients will be given a drug diary to document their use of IMP (Investigational Medicinal Product) and desmopressin.

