### Study procedure

See figure 2 and fiugre S1(online supplemental figure 1) for the study procedure.

*Baseline evaluation* (day 0, without IMP): Participants will complete the STAI-T, Hamilton Anxiety Inventory and TAS-20 questionnaires and perform computerised emotion recognition/empathy tasks (EmBody/EmFace, FERT, MET). Blood and urine samples will be collected for baseline analysis of hormones and metabolic markers. Participants will conduct self-reported questionnaires (STAI-S, BDI-II, AQ, PP-QoL, PROMIS), followed by an ad libitum meal to assess satiation. Close third-person assessments and questionnaires on sexual desire, behaviour (SDI-2, SBQ-G) and eating behaviour (TFEQ-18) may also be completed.

*Main visit 1* (day 1, with IMP): Participants will administer their first dose of intranasal OXT/placebo under supervision. Computerised tasks and additional questionnaires (STAI-S, subjective effects scales) will be completed at peak OXT concentration. Blood samples will be collected, and a second ad libitum meal will be provided to assess physiological and behavioural responses.

*Main visit 2* (day 28±2, with IMP): Primary outcomes (STAI-T and EmBody/EmFace tasks) will be completed. Participants will undergo final assessments, including blood sampling, IMP diary reviews, adverse event documentation and standardised questionnaires (eg, AQ, BDI-II, PP-QoL).

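### The protocol names two different recipients for the returned sprays, and one of them is the blinded investigator at the day-28 endpoint visit

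*Protocol article*

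**What the plan says.** Four parts of the protocol article bear on who may see the spray containers.

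- **Randomisation and blinding.** The allocation list "is concealed from participants, investigators, study nurses, study physicians, study psychologists and all outcome assessors", and these people stay blinded for the whole trial. The section explains why separate staff handle the product: "Because the container systems of the OXT and placebo sprays differ slightly in appearance". Those staff take no part in outcome or clinical assessment. Participants are told not to show or discuss their medication with blinded staff.
- **Blinding and dispensing.** "Used and unused study medications will be returned to the unblinded personnel".
- **Modification, preventive measures and concomitant treatments.** The cartons with the eight sprays "must be returned to the investigator for compliance control at the follow-up visit on day 28" (window ±2 days).
- **Control group.** The placebo is said to differ in its container system. The section then adds: "Packaging and labelling will ensure the sprays are indistinguishable to blinded study personnel".

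Study procedure places STAI-T, EmBody/EmFace, diary review and adverse event documentation at the same day-28 visit.

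**The concern.** The same returned items have two recipients, and one is a role the protocol declares blinded. The conflict also reaches the participant, who is told to keep the medication out of blinded staff's sight and, at the last visit, to hand it to one of them.

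By the protocol's own account the container is the weak point of the blind; that is why unblinded handlers exist. If a site follows the instruction to return the sprays to the investigator, that safeguard is lost at the visit where the treatment effect is measured. Knowledge or suspicion of allocation could then colour how the visit is run and how judged outcomes are recorded. Unblinding cannot be reversed once it has happened.

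**Working it through.** The point rests on reading the passages together; there is no stated figure to reproduce.

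**1. Is it the same material?** Yes. Blinding and dispensing covers all used and unused medication. The other section covers the full pack: "The empty carton containers with the eight sprays of the study medication must be returned to the investigator for compliance control". The second is a subset of the first, so the two instructions overlap completely for the sprays.

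**2. Is the second recipient blinded?** Yes. Investigators are named in the list of blinded roles, without exception and without an end date before day 28.

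**3. Could the return be handled without looking at the bottles?** Not if it serves compliance control. Inputs from Randomisation and blinding and Intervention group: eight bottles, 200 IU per bottle, 48 IU per day, 28 ± 2 days.

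- Supplied: 8 × 200 = 1,600 IU.
- Full adherence over 26 days: 26 × 48 = 1,248 IU, or 1,248 / 200 = 6.2 bottles.
- Full adherence over 30 days: 30 × 48 = 1,440 IU, or 1,440 / 200 = 7.2 bottles.
- Adherence of 50% over 28 days (the per-protocol threshold in Planned analyses): 0.5 × 28 × 48 = 672 IU, or 672 / 200 = 3.4 bottles.

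These figures assume nominal fill and no priming loss or waste. Even a fully adherent participant returns some product (about 0.8 to 1.8 bottles' worth), so a compliance check means inspecting the bottles. A closed carton tells the checker nothing about adherence.

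**4. Does the return coincide with outcome collection?** It falls at the same visit. The article does not say whether it comes before or after the assessments.

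**5. How many visits are covered?** Sample size calculations gives 112 recruited and 15% dropout: 112 × 0.85 = 95.2, close to the stated 94 evaluable. So about 95 completed day-28 visits, and never more than 112.

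**6. Which outcomes are exposed?**

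| Outcome at day 28 | How it is obtained | Exposure to an unblinded investigator |
|---|---|---|
| STAI-T | Questionnaire, scored from the participant's answers | Indirect, through conduct of the visit |
| EmBody/EmFace | Computerised three-option forced choice | Indirect, through conduct of the visit |
| Adverse events | Documented at the visit | Direct |
| Hamilton Anxiety Rating Scale | Rater not stated in the article | Direct if staff-rated (assumption) |

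**The case against.** **The two sections on blinding agree with each other.** The stray sentence stands in a section on concomitant treatment, and investigator may be shorthand for the site. That is plausible and suggests the intended procedure is sound. It does not remove the conflict: the sentence is mandatory in tone, ties the return to compliance control, and names a role that is expressly blinded.

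**Exposure is not shown.** The containers differ only slightly, nothing says that a viewer could tell which one holds oxytocin, and the return might follow the assessments. This stands, and it limits the claim to a risk that arises if the sentence is followed as written.

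**The primary endpoint is fairly robust.** One component is self-reported and the other is computerised. This also stands. A reader might infer that both components would be directly biased, or that handing back the sprays creates participant expectancy. The documents do not support this: the participant has used that container for four weeks, and staff do not score either measure by judgement.

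**The Control group section need not contradict the blinding section.** It says itself that the container systems differ, and its claim of indistinguishability can be read as referring to what blinded staff see from outside. That reading is coherent, so the sentence needs clarifying; it is not a second contradiction.

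**Later allocations.** Because blocks of four are fixed, a reader might infer that an investigator who sees returns could deduce a third of allocations: the fourth in a block always and the third in one block of three, (1 + 1/3) / 4 = 1/3. That is a ceiling. It needs every earlier allocation in the block to be known before the next randomisation, whereas returns come about 28 days after treatment starts. With no stratification factors, blocks may also run across centres. The figure is not part of this point.

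**Conclusion.** The contradiction is real and should be corrected. One instruction sends the sprays to a blinded investigator at the day-28 visit, the other sends them to unblinded staff, and a site cannot comply with both. The instruction covers about 95 completed visits, 112 at most.

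The consequence is conditional. It requires that a site follows the stray sentence, that the investigator sees the bottles, and that the slight difference can be recognised. If so, the likelier damage is to conduct of the visit, to adverse event recording and to the Hamilton scale if it is staff-rated. Any effect on the success rate would be smaller and indirect. No size of bias can be derived from the documents.

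A reader might conclude that the allocation is exposed. The article does not show that. Nor do its brevity on who supervises the first dose and its placebo ingredient list without a scent amount to further defects; a condensed article may leave such detail to the full protocol. The full protocol (V.5.0) is not shown. If it already names unblinded personnel as recipients, only the article needs correcting.

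**What to change.** 1. In the section on modification, preventive measures and concomitant treatments, replace the investigator as recipient. All used and unused sprays go only to the existing unblinded personnel, who carry out the compliance count and pass nothing but an adherence figure to blinded staff. This also supplies the count needed for the per-protocol set without showing anyone a container.
2. In Control group, state that indistinguishable refers to the outer packaging and labelling, so that it agrees with Randomisation and blinding on the differing container systems.
3. Send the corrected instruction to the two active centres and build it into set-up at the two planned ones. Ask the active centres which instruction they have followed so far, and record any return made to blinded staff.

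The cost is two sentences of text and a short site instruction. The unblinded staff already exist, and sample size, randomisation and analysis are unchanged.
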